## Abstract

**Background:** Social–emotional difficulties are a core symptom of autism spectrum disorder (ASD). Accordingly, individuals with ASD have problems with social cognition such as recognizing emotions from other peoples' faces. Various results from functional magnetic resonance imaging and electroencephalography studies as well as eye-tracking data reveal a neurophysiological basis of these deficits by linking them to abnormal brain activity. Thus, an intervention targeting the neural origin of ASD impairments seems warranted. A safe method able to influence neural activity is transcranial direct current stimulation (tDCS). This non-invasive brain stimulation method has already demonstrated promising results in several neuropsychiatric disorders in adults and children. The aim of this project is to investigate the effects of tDCS on ASD symptoms and their neural correlates in children and adolescents with ASD.

**Method:** This study is designed as a double-blind, randomized, and sham-controlled trial with a target sample size of 20 male participants (aged 12–17 years) diagnosed with ASD. Before randomization, the participants will be stratified into comorbid depression, comorbid ADHS/conduct disorder, or no-comorbidity groups. The intervention phase comprises 10 sessions of anodal or sham tDCS applied over the left prefrontal cortex within 2 consecutive weeks. To engage the targeted brain regions, participants will perform a social cognition training during the stimulation. TDCS-induced effects on ASD symptoms and involved neural circuits will be investigated through psychological, neurophysiological, imaging, and behavioral data at pre- and post-measurements. Tolerability will be evaluated using a standardized questionnaire. Follow-up assessments 1 and 6 months after the intervention will examine long-lasting effects.

**Discussion:** The results of this study will provide insights into the changeability of social impairments in ASD by investigating social and emotional abilities on different modalities following repeated sessions of anodal tDCS with an intra-simulation training. Furthermore, this trial will elucidate the tolerability and the potential of tDCS as a new treatment approach for ASD in adolescents.

**Clinical Trial Registration:** The study is ongoing and has been registered in the German Registry of Clinical Trials (DRKS00017505) on 02/07/2019.

## Introduction

One out of 54 children fulfills the diagnostic criteria for autism spectrum disorder (ASD) (1), with boys being affected three to four times as often as girls (2). ASD is a neurodevelopmental disorder characterized by social and communicative deficits and repetitive, stereotyped behaviors, ranging over a wide spectrum with different degrees of impairment [International Classification of Diseases ICD-10; (3)].

As there is currently no cure for ASD, psychosocial and pharmacological treatments share the aim to ameliorate the core symptoms and enable a life as independent as possible (4). Psychosocial interventions show positive effects on intellectual and adaptive functioning (5), but suffer from limited support from randomized controlled trials (RCTs). Strongest evidence exists for the effectiveness of interventions that focus on early parent–child interactions (6, 7). Furthermore, there is no pharmacological treatment for the core symptoms of ASD and medication is mainly used for the therapy of commonly co-occurring disorders such as attention-deficit/hyperactivity disorder (ADHD) or depression (6). The need for efficient and affordable new treatment methods also becomes evident when assessing quality of life, employment, independency, social relationships, and mental and physical health in adults with ASD, which were found to be poor despite average cognitive functioning (8, 9). Thus, specifically targeting the mechanisms underlying the social–emotional dysfunctions in ASD can form the basis of new and viable treatment methods.

Social–emotional difficulties include pronounced impairments in empathy, a central prerequisite for social interactions. To be able to understand what others are feeling and to react appropriately to their emotions, it is often necessary to recognize the expressed emotion from others' faces. The ability to discriminate the six basic emotions (happy, sad, fear, anger, disgust, and surprise) is usually acquired in the first year of life (10), whereas the ability to discriminate more complex emotions improves until adulthood (11). It has been repeatedly shown that people with ASD have a deficit in the ability to recognize the emotions of others (12, 13). Moreover, results from neurological and electrophysiological studies show clear differences in automatic emotion recognition processes between ASD and typically developing children (14).

Another factor influencing social interactions is the direction of gaze (15). Eye-tracking reveals that children with ASD show aberrant patterns of gaze and fixation times when seeing human faces (16, 17) and eye gaze abnormalities have even been proposed as a robust biomarker for ASD (16). Moreover, dysfunctions in several brain regions including the dorsolateral prefrontal cortex (DLPFC) are involved in the development of this aberrant gaze behavior. In typically developing individuals, direct gaze leads to an enhanced response in brain areas important for empathic processes like theory of mind (ToM). In contrast, individuals with ASD show the same response when the gaze is averted and respond to direct gaze with an abnormal activation of the ToM network [medial prefrontal cortex (MPFC), temporoparietal junction, posterior superior temporal sulcus region, and amygdala] (15). These regions are also part of the social brain network (SBN) (18, 19).

Research regarding the neural underpinnings of behavioral social problems in ASD found evidence for alterations within the SBN in structural and functional magnetic resonance imaging (MRI) studies (20). Furthermore, structural MRI studies showed abnormalities in gray matter volume and white matter structure in short-distance tracts in the SBN, as well as an association between these abnormalities and social malfunctioning in ASD (21–24). Task-related fMRI studies in individuals with ASD revealed atypical activity and connectivity in social brain regions during the processing of social stimuli (25). For instance, processing of emotional facial expressions was associated with reduced activity in several brain regions important for interpersonal interactions, including the amygdala, MPFC, ventrolateral prefrontal cortex, and superior temporal sulcus region in individuals with ASD compared with typically developing individuals (26). Neuroimaging results show that the most consistently activated brain regions in ToM tasks are the medial prefrontal and orbitofrontal cortices (27). Within the ToM network, reduced functional connectivity in persons with ASD was detected (15). In detail, the functional connectivity between the MPFC and the posterior cingulate cortex (PCC) has repeatedly been shown to be lower in individuals with ASD (28, 29). A weaker connectivity between these regions is correlated with more serious social impairments [see (29)]. Both the MPFC and the PCC are part of the default mode network (DMN), which is involved in complex emotional and social processes such as ToM and self-referential thoughts (30, 31). Functional connectivity of DMN regions has been shown to be altered at rest and reduced in several social tasks such as face processing in adolescents and adults with ASD (28, 32). While the functional connectivity between the DMN nodes normally increases with age, the development of long-distance functional connectivity in the DMN cannot be observed in adolescents with ASD (28, 33). Also, brain regions important for social interactions outside the DMN exhibit reduced activity and functional connectivity during resting state (20). Individuals with ASD showed, compared with typically developing individuals, a weaker functional connectivity between the amygdala and the ventromedial prefrontal cortex (34) and a reduced connectivity within the lateral occipital cortex, which was associated with symptom severity (35). Thus, it appears that neurophysiologically based interventions should target the MPFC as a potential mediator for the reduction of ASD symptoms.

Contrary to fMRI, electroencephalography (EEG) allows for calculating the functional connectivity of the brain based on absolutely quantifiable rather than relative measures. In ASD, resting-state EEG studies suggest a reduced long-range connectivity between frontal lobe and other cortical regions and short-range overconnectivity (36, 37). Regarding frequency bands, decreased power in alpha is the most consistent finding (36, 38), which is thought to be associated with inhibitory control deficits in ASD (36).

Neuromodulation constitutes, alongside psychosocial interventions and psychopharmacology, the third pillar of therapeutic interventions in psychiatry. Transcranial direct current stimulation (tDCS) in particular is a non-invasive neurophysiological method, which has the potential to modify brain function by affecting neuronal resting membrane potentials (39, 40). It affects neuronal excitability on a sub-threshold level without eliciting action potentials (40–42). Depending on the goal of the intervention, anodal or cathodal stimulation can be used to either enhance or reduce neuronal excitability and thereby modulate processes related to the target brain region in the desired direction (43). The effects of direct current stimulation elicits a polarity-dependent facilitation or inhibition of the spontaneous neuronal firing rate (40, 43, 44). Post-stimulation effects of tDCS are contingent on the duration of the stimulation and last from several minutes up to some hours (40, 45). Studies investigating the effects of tDCS on neural activity showed that direct current can modulate cortical connectivity in the brain (46) and induce changes in the alpha frequency band during and after the stimulation (47–49). Moreover, fMRI studies found changes in brain connectivity in both task-related and resting-state networks after the application of tDCS (50–53). Brain stimulation is more effective and causes more long-lasting plastic changes in already activated neural circuits (54). Additionally, aftereffects of tDCS were shown to depend on the emotional and physiological state during stimulation (41). Given these findings, intra-stimulation engagement tasks are used to enhance the effects of tDCS [e.g., (55, 56)].

Therapeutically, tDCS is used to alter local neuronal excitability that is assumed to be in a dysfunctional hypo- or hyperactive state (45). Effects of the stimulation expand by changes in the neural network into more distant regions and lead to reorganization of neuronal circuits (45, 57). Due to encouraging results in the treatment of various neuropsychiatric disorders in adults (58–61), tDCS has gained attention in the treatment of childhood and adolescent neuropsychiatric disorders over the past years (45, 62–64).

Regarding the use of tDCS in children with ASD, 12 articles have been published to date (65–76). Among these, four are randomized, double-blind, sham-controlled studies; the remaining articles comprise experimental, quasi-experimental, and pilot studies, a case series, and a case study. Outcome measurements, number and details of stimulation sessions, and control conditions vary across the studies [for reviews see (77, 78)]. Therefore, the current evidence is sparse and methodologically incomparable (79). Nevertheless, these studies point toward positive effects of tDCS in the treatment of ASD showing an improvement in ASD symptoms such as socialization, sensory awareness, repetitive behaviors, and behavioral problems (65, 68, 70, 76) as well as in cognitive abilities often impaired in individuals with ASD (71, 74). The available results not only provide indications for significant symptom reductions maintained for 6 months (68) but also emphasize the necessity of further research (70, 79). The potential of tDCS to counteract ASD-specific aberrant brain activity was highlighted by studies showing modulation of long-distance connectivity (66), an increase in functional connectivity in the alpha band (68, 80), increasing connectivity between the hemispheres within alpha and induced neuroplastic changes (75). Moreover, studies report a reduction in ASD symptoms that were associated with an increase in the peak alpha frequency band in resting-state EEG (76) and increasing EEG complexity (72) after tDCS stimulation. These studies as well as the majority of the present tDCS studies in children and adolescents with ASD report reduced ASD symptoms after anodal stimulation with the anode placed over the DLPFC (77). However, none of the studies used a simulation-based approach to evaluate the peak magnitudes of the electric fields and to define the stimulation target. TDCS applied over this commonly used stimulation site is able to increase the functional connectivity between the MPFC and the PCC in healthy adults (51) as well as in individuals with ASD (81). Taken together, both theoretical considerations and empirical findings regarding the pathophysiological signature of ASD lead to the proposition that tDCS can be used to alter dysfunctional patterns of brain activity.

The goal of the present study is to investigate the clinical and scientific significance of tDCS for improving social cognition abilities in ASD with a clear neurobiological rationale. Therefore, the planned study will (1) examine tDCS-related changes on reported symptomatic changes, behavior, brain activity, and connectivity; and (2) explore the long-term effects of tDCS in ASD and thereby evaluate tDCS as a cost-effective, time-efficient treatment option for children and adolescents with ASD.

## Methods and Analysis

The study is designed as a randomized, double-blind, sham-controlled clinical trial with two follow-up measurements 1 and 6 months after the last stimulation session, respectively.

### Participants

Measurements and interventions will be carried out at the Department of Child and Adolescent Psychiatry at the Medical University of Vienna, Austria. The participants will be recruited from the outpatient clinic and from local institutes for individuals with ASD.

#### Sample Size Calculations

Power analysis was done with G^*^Power version 3.1.9.2 (82) to detect a difference in the primary outcome [SRS, (83)] calculating repeated measures ANOVA considering an effect size *f* of 0.25, a power of 80%, and an α of 0.05. Previous studies in children with ASD have shown larger effect sizes for tDCS (63). A sample size of 20 participants (*N* = 20) will be necessary to report medium effect sizes on the primary outcome. Analyses of secondary outcomes were not included in the power analysis and therefore considered underpowered.

#### Randomization

A total of 20 male participants will be included. To balance the experimental and control group with respect to comorbidities, all participants will be stratified into one of three subgroups based on their clinical presentation: subgroup A for participants without comorbidity, subgroup B for participants with depression as primary comorbidity, and subgroup C for participants with ADHD and/or conduct disorder as primary comorbidity. After subgroup stratification, the participants will be randomly allocated to the active condition or the sham condition by assigning a code to each participant. To ensure a quick study start for the participants after enrollment, a block randomization design will be used.

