### Statistical Analysis

For the statistical analyses, repeated measures analysis of variance (ANOVA) and hierarchical linear models (HLMs) will be used. A 4 × 2 mixed ANOVA (primary outcome as dependent variable) with *Time* (pre vs. post vs. follow-up 1 vs. follow-up 2) as the within-subjects factor and *Group* (experimental vs. control group) as the between-subject factor will be conducted to investigate an interaction between time and group. In order to test specific effects, *post-hoc* tests will be employed. A HLM will be formulated to investigate time-dependent changes and group differences in task performance across stimulation sessions. A *p* < 0.05 will be considered statistically significant. Analysis will be conducted in *R* (121).

For the eye-tracking data, analysis of fixation duration and pupil dilation will be done in Tobii Studio 3.4.5 (107) following the preprocessing pipeline of other studies using eye-tracking to investigate emotion recognition and social cognition in adolescents with ASD [for the ERT (17) and for the MASC (106)]. These results in a fixation duration on the specified area of interest (AOI) and a measure of average pupil dilation per video. Further analysis regarding pre–post comparisons of AOIs and pupil dilation will be done in *R* (121) using linear models.

For the EEG data, we will employ the *MNE* library (122) written in *Python* (123) to execute data pre-processing, segmentation, and frequency and connectivity analyses. The raw EEG data of each participant will be segmented into epochs of 2 s. A multi-taper method with adaptive weights will be applied to each epoch to obtain power spectral density (PSD) values in each frequency band of interest. Frequency bands of interest will be delta (0.5–4 Hz), theta (4–8 Hz), and alpha (8–12 Hz). Subsequently, PSD values in each frequency band will be averaged across epochs separately for each participant, measurement occasion, and experimental condition.

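### Allocation is stratified by comorbidity but the primary Time × Group ANOVA leaves the stratum out; if the comorbidity groups change differently on the SRS, the test becomes conservative and loses some power

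*Protocol article*

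**What the plan says.** In the Protocol article, the Randomization section states that "all participants will be stratified into one of three subgroups based on their clinical presentation" and gives the aim of the stratification as "To balance the experimental and control group with respect to comorbidities". The three subgroups are no comorbidity, depression as primary comorbidity, and ADHD and/or conduct disorder as primary comorbidity. Assignment to active or sham follows within this scheme, and "a block randomization design will be used". The total is 20 participants. No block size, allocation ratio or expected stratum size is given.

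The Statistical Analysis section defines the primary analysis as "A 4 × 2 mixed ANOVA (primary outcome as dependent variable) with *Time* (pre vs. post vs. follow-up 1 vs. follow-up 2") and names a single between-subject factor, Group ("experimental vs. control group) as the between-subject factor"). The effect tested is the Time × Group interaction. Comorbidity appears neither as a factor nor as a covariate.

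**The concern.** Balancing the arms within strata removes stratum differences from the comparison of arms. If the model omits the strata, any stratum variation relevant to the tested effect stays in the residual. The residual mean square is then larger than the true uncertainty of the comparison, so the F test rejects too rarely under the null and has less power under the alternative. With 20 participants in total, a loss of a few points would be worth avoiding.

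The question is which stratum variation is relevant to this particular test, and how much it could cost.

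**Working it through.** **Inputs from the article.** N = 20, two groups, m = 4 occasions, f = 0.25, α = 0.05, power 80%.

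**Assumptions, because the article gives no figures.** 1:1 allocation; strata of 8, 6 and 6, split evenly between arms; SD 1; equal correlation ρ = 0.5 between occasions; no missing data; treatment effect a step of 1.05 SD present at post and both follow-ups. Stratum differences in change follow the same step pattern, with scores −1, 0, +1 times d SD.

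**1. The plan's own figure.** For the interaction, λ = f²·N·m/(1 − ρ), df1 = 3 and df2 = (20 − 2)·3 = 54.
- ρ = 0.5: λ = 0.0625·20·4/0.5 = 10, power 72.7%; 24 participants would be needed for 80%.
- ρ = 0.6: λ = 5/0.4 = 12.5, power 82.7%; 20 participants suffice.

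So N = 20 can be reached with four occasions at ρ of about 0.6, but the article does not state ρ or the number of occasions used. The present point does not depend on it.

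**2. Differences in level.** The interaction is built from within-subject contrasts. A stratum difference that is constant over time drops out of both the interaction mean square and its error term. Simulation of the stated ANOVA (6,000 trials per setting) with strata 0, 1 or 2 SD apart in level gave type I error of 5.0–5.4% without the stratum terms and 5.2–5.6% with them. Power was about 63–64% either way.

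**3. Differences in change.** These do not drop out.
- Time pattern (0, 1, 1, 1), mean 0.75: sum of squared deviations = 3·0.25² + 0.75² = 0.75.
- Stratum scores, mean (−8 + 6)/20 = −0.1: sum of squared deviations = 14 − 20·0.01 = 13.8.
- Extra error sum of squares = 13.8·0.75·d² = 10.35·d².
- Relative to the true error variance (1 − ρ = 0.5) on 54 df: 10.35·d²/(54·0.5) = 0.383·d².

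The error mean square is therefore inflated by about 3.4%, 9.6% and 24.5% for d = 0.3, 0.5 and 0.8.

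**4. Effect on the test (same simulation).**

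| d (SD per stratum step) | Type I, without terms | Type I, with terms | Power, without | Power, with |
|---|---|---|---|---|
| 0 | 5.4% | 5.6% | 64.3% | 64.0% |
| 0.3 | 4.1% | 4.9% | 60.8% | 62.1% |
| 0.5 | 3.4% | 5.0% | 57.6% | 62.5% |
| 0.8 | 2.4% | 5.1% | 50.0% | 63.1% |

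A repeat of the simulation gave type I error of about 3.9%, 4.1% and 2.3% and power of about 61%, 60% and 49% without the terms, against about 62–64% with them.

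Direct calculation agrees. The treatment noncentrality is 1.05²·(20/4)·0.75/0.5 = 8.27, and the omitted stratum × time effect adds noncentrality 10.35·d²/0.5 = 20.7·d² to the error sum of squares. This gives type I error of 4.5%, 3.7% and 2.2%, and power of 61.6%, 58.2% and 50.2% against 63.1% with the terms.

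**5. Cost of adjusting when nothing is gained.** Error df fall to (20 − 2 − 2)·3 = 48. At f = 0.25, power goes from 72.7% to 72.3% (ρ = 0.5) or from 82.7% to 82.4% (ρ = 0.6).

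**The case against.** The case for leaving the model as it is has four parts.

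- **The loss is conditional.** It arises only if comorbidity predicts change in the SRS, and nothing in the article says that it does. This stands. At 0.3 SD per step the loss is only about 1 point; it becomes material at 0.5 SD and above, and those values are assumed.
- **The aim was balance.** A reader might infer that the stratification was meant to gain precision which the analysis then throws away. The Randomization section gives balance as its aim, and the allocation delivers that whatever model is fitted. That inference is not supported. The argument for including the stratum is only that the analysis should reflect how participants were allocated.
- **Cells may be very small.** Twenty participants in three strata can leave only a few per arm in a stratum, so omitting the factor is a defensible choice. This is a fair reason to ask for a justification instead of the term. It is weakened by the small cost found in step 5.
- **The article is condensed.** Covariates are often left to the analysis plan, which is not shown. That would cover a silent text. Here, however, the between-subject structure of the primary model is stated, and it contains Group alone. The same criticism cannot be made of the hierarchical model for task performance, which is only sketched.

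**Conclusion.** The point holds in a limited form. The stated primary model omits the factor by which allocation is stratified. This matters only through a stratum × time effect, and then only by making the test conservative. Under the assumptions listed, differences in change of 0.3, 0.5 or 0.8 SD per stratum step bring the type I error to about 4%, 3.5–4% or 2.3% and cost about 1, 4–5 or 13 points of power. With no such difference nothing is lost.

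Two stronger readings are tempting. A reader might infer that the primary test is invalid or could produce false positives; in none of the scenarios did omission raise the type I error above that of the adjusted test, and with balanced strata the omitted variation can only enlarge the error term. A reader might also infer that the error estimate is wrong in every case; it is not, because stratum differences in SRS level cancel and the article gives no evidence of differences in change. The stratum sizes, correlation, step size and range of d are all assumptions. The priority is minor.

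**What to change.** Add the three-level comorbidity stratum and its interaction with time to the primary SRS model, or state why it is left out. A stratum main effect alone would not change the Time × Group test; the stratum × time term is what matters. Make the change before unblinding, so that the adjustment is not post hoc.

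The cost is six error degrees of freedom (54 to 48), which is less than 1 point of power if the strata do not differ in change. Sample size, allocation and data collection stay as they are. If the full analysis plan already contains these terms, only the description in the article needs to be aligned.
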